### Randomisation and blinding

The present study is a protocol for a single-blind randomised controlled trial in which each group of participants is exposed to only one of the study interventions. Patients will be randomly allocated to robotic-assisted TKA or to conventional freehand TKA. All patients in whom a TKA is indicated will be sequentially allocated in a 1:1 ratio to surgeons who perform robotic-assisted TKA or to those who perform conventional freehand TKA at the time of their outpatient appointment. All patients, irrespective of their allocation, will follow the same clinical, imaging, and anaesthesiologic pre- and post-surgical pathways. Patients will be blinded to the allocation until the first postoperative days. Surgeons and personnel involved in the clinical management of the patients will be unblinded to the allocation. Data curacy and collection will be conducted by two assessors blinded to group allocation and not involved in the clinical management of the patients. Assessors will retrieve patient data at the following follow-up times: admission, perioperatively (from access to discharge), at 6 weeks, 12 months, and every 24 months postoperatively. Data from patients will be collected once the learning curve has been reached.

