### Eligibility criteria

The inclusion criteria are: (1) age above 18, (2) ability to consent, (3) symptomatic knee osteoarthritis stage II to IV according to the Kellgren-Lawrence classification [16] (Table 1). The exclusion criteria are: (1) acute or chronic inflammatory diseases, (2) neoplastic diseases, (3) pregnancy and lactation, (4) uncontrolled coagulopathy, (5) abnormal cell count, (6) severe peripheral neuropathy, (7) vascular diseases, (8) peripheral ulcers, (9) other condition that could influence the results of the present study.

**Table 1 Tab1:** Kellgren Lawarence classification

Stadium	Grade of OA	Description
0	No evidence of OA	No radiologic evidence of OA
I	Minimal OA	Doubtful narrowing of joint space and possible osteophytic lipping
II	Mild OA	Definite osteophytes and possible narrowing of joint space
III	Moderate OA	Moderate multiple osteophytes, definite narrowing of joint space, some sclerosis, and possible deformity of bone ends
IV	Severe OA	Large osteophytes, marked narrowing of joint space, severe sclerosis, and definite deformity of bone ends

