### Surgical procedures and rehabilitation protocol

All patients shall receive a 1.5 g single administration of intravenous cefuroxime at induction of anaesthesia. A femoral nerve block shall be used for pain control and maintained for 48 h. A tourniquet 120 mmHg over the systolic arterial pressure shall be used. All surgeries will be performed using a standard medial parapatellar approach. A restricted kynematic alignment will be performed to all TKA. All components will be implanted following manufacturer instructions using the Smith & Nephew Legion Genesis II, with a posterior stabilised polyethylene liner insert. Both femoral and tibial implants will be cemented using Palacos cement (Heraeus Medical GmbH, Wehrheim, Germany). At the end of the procedure, 1 g of tranexamic acid will be injected intra-articularly. One closed suction deep drain and one open suction subcutaneous drain shall be used for the first 48 h. Anti-thrombotic prophylaxis with Rivaroxaban, 10 mg daily for 6 weeks, will start 12 h after the index procedure. Physiotherapy will follow standard protocols [21]. Patients will be followed by a team of physiotherapists during hospitalization from the first postoperative day. In the absence of complications or other medical reasons who prevent discharge, the standard length of hospitalisation at our institution is 5 days. Moreover, from POD-2, each patient will undergo two sessions of physiotherapy daily using continuous passive motion (CPM) for 60 min per session to flex and extend the knee joint. The physiotherapist will increase the range of motion at each. Patients shall be discharged when they shall have reach at least 80° of flexion. Starting from POD-2, patients will start to walk under physiotherapeutic supervision, and on POD-4 they shall start to ascend and descend stairs. A personalised outpatient or inpatient rehabilitation program will be set for every patient for a minimum of 3 weeks. Deviation from the planned surgical procedure and rehabilitation protocol shall warrant exclusion from the study.

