Approximately 2000 TKAs are performed each year at our institution, which has been accredited by “Endocert” since 2016. The EndoCert initiative represents the first worldwide certification system of medical centres for total joint replacement and was established in Germany in 2012. The EndoCert aims to maintain quality standards in primary and revision arthroplasty. The associated centres also develop and define standards as well as treatment processes, and they are subject to continuous re-certification [29, 30]. All surgeries shall be conducted by six surgeons in a highly standardized fashion. All surgeons have obtained the certificate of the senior operator of EndoCert, and are well beyond their learning curve, having each performed more than 250 knee arthroplasties.

Some limitations of the present protocol must be acknowledged. The use of the CORI system during TKA requires special instrumentation, training and organisation. Surgery with CORI might initially require a longer time, and the surgical slots will be reserved for a longer time. Therefore, the healthcare staff involved in the clinical management of the patients will not be blinded, increasing the risk of performance bias. Patients will be informed in regard to the nature of the surgery (freehand or robotic) during their postoperative inpatient stay. According to current German legislation, all patients will receive a discharge letter with a description of the surgical intervention. In this instance, patients will have to be aware of their allocation, impacting on detection bias. The Likert-like questionnaire used in the present study is routinely administered at our institution to patients who undergo TKA to rate the function of the knee. Investigations are ongoing to validate this questionnaire in the clinical setting.

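### Allocation is called random, but the only mechanism described is sequential 1:1 assignment at the outpatient visit; read literally, that is foreseeable alternation

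*Protocol article*

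**What the plan says.** In the protocol article, the section Randomisation and blinding makes two statements in adjacent sentences. The principle is "Patients will be randomly allocated to robotic-assisted TKA or to conventional freehand TKA". The mechanism is that patients are "sequentially allocated in a 1:1 ratio to surgeons who perform robotic-assisted TKA or to those who perform conventional freehand TKA", and this happens "at the time of their outpatient appointment". The sentence on mechanism opens with "All patients in whom a TKA is indicated will be", so the queue is defined by the surgical indication, not by consent or confirmed eligibility.

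Four other places bear on the point:

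- Participants: written consent is obtained preoperatively. Its order relative to allocation is not given.
- Eligibility criteria: exclusion (9) is an open category, "other condition that could influence the results of the present study". No decision-maker and no time point is named for any criterion.
- Randomisation and blinding: "Surgeons and personnel involved in the clinical management of the patients will be unblinded to the allocation". Patients are kept blinded until the first days after surgery.
- Discussion: "All surgeries shall be conducted by six surgeons in a highly standardized fashion". The number of surgeons per arm is not stated.

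The Introduction, Randomisation and blinding, and the Discussion all describe the study as a randomised controlled trial. Study protocol says it will follow SPIRIT 2013.

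**The concern.** Whether assignment is random or systematic decides what kind of study this is. The text gives the label of one and the procedure of the other. If the procedure is followed as written, the next arm can be known before a patient is entered. Entry decisions can then depend on it, consciously or not: whom to approach, whether a comorbidity falls under exclusion (9), whether to confirm the patient as eligible.

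Because the queue is everyone with an indication, a 1:1 split of the queue does not guarantee comparable groups among those who end up in the trial. What matters is who is taken from each side, and as written that can be settled after the arm is known. Statistical analysis plans unpaired t-tests and chi-squared tests. Covariate adjustment, were it added, could not remove selection on prognosis that was not measured.

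**Working it through.** **The plan's own figure.** Sample size evaluation gives 198 per group (396 in total) from a 5-unit difference, SD 20, power 80% and 5% significance. With n = 2·SD²·(z_α + z_β)²/distance²:

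- One-sided 5%: 2·400·(1.645 + 0.842)²/25 = 197.8, rounded up to 198. This reproduces the plan. A 10-unit margin with a true difference of 5 leaves the same 5-unit distance and also gives 198.
- Two-sided 5%: 2·400·(1.960 + 0.842)²/25 = 251.2, rounded up to 252. This does not reproduce it.

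The point here does not depend on the sample size; it only supplies N = 396.

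**The sentences side by side.**

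| Question | Principle | Mechanism |
|---|---|---|
| How is the arm chosen? | At random | In sequence, 1:1 |
| Assigned to what? | Technique | Surgeon group |
| Who is assigned? | Patients | Everyone with an indication |
| When? | Not stated | Outpatient appointment |

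The text does not say how the two sentences fit together.

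**Predictability of the next arm over 396 patients.**

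- Strict alternation (assumption: this is what sequential means here). The first arm is a coin-toss guess and the other 395 are certain: (395 + 0.5)/396 = 0.9987, or 99.9%. A longer queue only moves this closer to 100%.
- Simple randomisation: 50%.
- Permuted blocks, when all past assignments are known and the guesser picks the arm with fewer patients so far (1,000 simulated runs each): about 71% with fixed blocks of 4, and about 68% with block sizes 4, 6 and 8 mixed at random.

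**What bias could follow (hypothetical).** Suppose a share s of one arm consists of patients selected for that arm whose expected WOMAC differs by d points from the patients they displace, and the other arm is unaffected. The contrast shifts by s·d. With s = 0.10 to 0.20 and d = 10, both assumed, that is 1 to 2 points, or 20% to 40% of the 5-unit planning difference. If the other arm is affected equally in the opposite direction, the shift doubles to 2 to 4 points. With s = 0 it is zero. The documents support no particular value of s or d.

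**The case against.** **Sequentially need not mean alternately.** It can mean in order of presentation, with each arm read from a random list, and such a list can be concealed. The section does say that allocation is random. This is also a condensed article, so the sequence generator and the concealment method may stand in a fuller document, and their absence is no fault. All of this stands, and it makes the predictability figure conditional. It does not remove the point, because the article does not merely leave the mechanism out: it states one, and that one conflicts with the label.

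**A reader might infer that unblinded surgeons decide eligibility, or that staff can rearrange appointments to suit an arm.** The documents say neither. Nobody is named as judging the criteria, and nothing is said about who books appointments. Nor does the statement on unblinded staff show foreknowledge. It means that they know the arm a patient has been given, which a surgeon cannot avoid in a trial of technique. Foreknowledge of the next arm would come from a systematic rule applied to visible past assignments.

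**Consent is written and preoperative, and patients are blinded until after surgery.** A patient's own decision should therefore not depend on the arm. That is fair, but it does not cover staff decisions on whom to invite and whom to exclude. The order of consent, eligibility and allocation is unstated; it is not shown to be wrong.

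**The bias figures are invented inputs.** Correct. They illustrate scale and are not an estimate.

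**Conclusion.** The point holds as a conflict in the stated design and should be fixed. The article labels allocation random and then describes a sequential 1:1 rule. On the literal reading, the next arm is foreseeable about 99.9% of the time to anyone who knows the last one, and the study is quasi-randomised. On the milder reading, the text misdescribes a sound procedure. Either way it cannot stand.

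The 99.9% rests on the assumption of strict alternation, and the size of any resulting bias is unknown. The text leaves room for consent and eligibility, including the open-ended exclusion (9), to be settled after the arm is known; it does not establish that this happens or who would do it. The documents therefore do not support the stronger conclusion that the trial is in fact alternated and steered by its surgeons.

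A related route for selection after allocation lies in Surgical procedures and rehabilitation protocol: "Deviation from the planned surgical procedure and rehabilitation protocol shall warrant exclusion from the study". It is a separate matter, but concealed allocation alone would not close it.

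**What to change.** In Randomisation and blinding, replace the sentence on sequential assignment with text to this effect: *Written consent is obtained and all eligibility criteria, including exclusion (9), are confirmed and recorded first. A computer-generated 1:1 random sequence, concealed from recruiting staff (for example by central release), is then opened for that patient. Surgeon and operating slot follow from the result.*

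Exclusion (9) need not be deleted if it is settled and recorded before allocation. If blocks are used, vary their sizes at random and withhold them from recruiting staff, since past assignments are visible to the clinical team and some predictability remains (about 68% to 71% in the check above).

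If assignment is truly sequential, describe the study as quasi-randomised throughout. If some patients have already been allocated that way, describe them as quasi-randomised and report how many there are.

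Cost: a protocol amendment, a generated list, and slightly less scheduling freedom because surgeon and slot are booked after allocation. Recruitment was planned from January 2023 to January 2033, so a change can protect later entries but does not repair allocations already made.

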### Eligibility criteria

The inclusion criteria are: (1) age above 18, (2) ability to consent, (3) symptomatic knee osteoarthritis stage II to IV according to the Kellgren-Lawrence classification [16] (Table 1). The exclusion criteria are: (1) acute or chronic inflammatory diseases, (2) neoplastic diseases, (3) pregnancy and lactation, (4) uncontrolled coagulopathy, (5) abnormal cell count, (6) severe peripheral neuropathy, (7) vascular diseases, (8) peripheral ulcers, (9) other condition that could influence the results of the present study.

**Table 1 Tab1:** Kellgren Lawarence classification

Stadium	Grade of OA	Description
0	No evidence of OA	No radiologic evidence of OA
I	Minimal OA	Doubtful narrowing of joint space and possible osteophytic lipping
II	Mild OA	Definite osteophytes and possible narrowing of joint space
III	Moderate OA	Moderate multiple osteophytes, definite narrowing of joint space, some sclerosis, and possible deformity of bone ends
IV	Severe OA	Large osteophytes, marked narrowing of joint space, severe sclerosis, and definite deformity of bone ends

### Outcomes of interests

The primary outcome of interest is to compare robotic-assisted TKA using CORI robotic system versus conventional freehand arthroplasty. The surgical duration, length of the hospitalisation, blood analyses, implant positioning, blood units transfused, ROM, PROMs, and complications will be collected from both groups and compared as shown in Fig. 1.

**Fig. 1 Fig1:**
[figure not shown]
Set up of follow-ups and data extraction

The second outcome of interest will be to compare implant positioning between robotic and conventional TKA. Implant positioning will be evaluated using anteroposterior plain radiographs of the leg using the software MediCAD Knie 2D (mediCAD Hectec GmbH, Altdorf, Germany), which is used to perform surgical planning of hip, knee, shoulder, trauma and spine surgery. The imaging references to assess implant positioning are shown in Fig. 2. An explanation of the main imaging references used is shown in Table 2.

**Fig. 2 Fig2:**
[figure not shown]
Imaging references, illustrating the main axes and reference angles

**Table 2 Tab2:** Imaging parameters

Abbreviation	Definition	Mean	Range	Description
mLDFA	Mechanical lateral distal femoral angle	88°	85–90	Angle between the lateral femur and the proximal femoral joint
mLPFA	Mechanical lateral proximal femoral angle	90°	85–95	Angle between the mechanical femoral shaft axis and the orientation line through the centre of the femoral head and the tip of the greater trochanter
m/aLDTA	Mechanical/anatomical lateral distal tibial angle	89°	86–92	Angle between the mechanical axis of the tibia and the tibial plafond, measured on the lateral side
m/aMPTA	Mechanical/anatomical medial proximal tibial angle	87°	85–90	Angle between the mechanical axis of the tibia and the tibial plateau knee joint line, measured on the medial side
JLCA	Joint line convergence angle	1.5° medial	0–3	Interaction of the intra-articular deformity arising from the osteoarthritis and the surrounding soft tissue laxity
MAD	Mechanical axis deviation	10 mm medial	3–17	Distance from the centre of the knee joint and the line of the mechanical axis
AMA	Anatomical-mechanical-angle	6°	5–7	Angle between anatomical and mechanical femoral axes

### Data to be collected

On admission, the demographic information (age at surgery, BMI, sex), stage of OA according to the Kellgren-Lawrence classification [16], PROMs, and blood values of each patient will be collected on admission. Concerning the blood values, the haematocrit, haemoglobin, and C-reactive protein (CRP) will be collected preoperatively, on the first and fifth postoperative days. The blood tests will be conducted on admission, postoperative day (POD) 1 and 5 by dedicated healthcare personnel. To assess ROM, the neutral-zero method shall be used [17], using a standard baseline plastic 360-degree plastic pocket goniometer with flexion-hyper extension gauge (ProHealthcareProducts.com, Park City, US). ROM surgery will be assessed by moving the foot from a neutral starting position (neutral position in extension) in flexion and extension. ROM data will be collected on admission, on POD 1, 2, 3, 4, 5, and at each follow-up appointment by medical personnel who has not performed the index surgery. The German version of the Western Ontario and McMaster Universities Osteoarthritis Index (WOMAC) [18] and the visual analogue rating scale of health-related quality of life [19] will be used to rate the clinical outcomes. The patients will complete the questionnaires at admission and at each post-operative follow-up appointment. To evaluate the activity level of the patients included in the trial, the German version of the Tegner score will be administered [20]. In addition, a further seven questions Likert-like questionnaire shall be administered to all patients. This questionnaire is routinely used at our institution to rate the function of the knee in patients who undergo TKA. The questionnaire enquires about the activities related to the knee, post-operative overall patient satisfaction, patient satisfaction with the function of the knee, and information concerning walking distance. The Likert-like questionnaire is reported in Fig. 3, and the German version is available in Additional file 1.

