## Introduction

Total knee arthroplasty (TKA) aims to restore knee pain and function, and improve the quality of life of patients [1–3] with end-stage osteoarthritis (OA) [4]. However, between 2 and 20% of patients who underwent TKA reported restricted motion and anterior knee pain [1, 5, 6]. These complications could arise from a non-optimal alignment of implant components [2, 7]. In this context, the introduction of robotic-assisted TKA is supposed to improve the accuracy of component positioning and to match more precisely patients’ anatomy and biomechanics [8]. Robotic TKA has been introduced to improve component alignment [9–11], impacting favourably on postoperative pain, hospitalisation, long-term implant survival [12, 13], and patient satisfaction [14]. However, the advantages of robotic surgery over conventional freehand TKA are still unclear, and high quality clinical investigations on large scale are necessary. Therefore, a single-blind randomised controlled trial will be conducted to evaluate TKA using the CORI robotic system (Smith & Nephew PLC, London, Great Britain). The primary outcome of interest is to compare robotic-assisted TKA versus the conventional freehand TKA in terms of patient-reported outcome measures (PROMs), length of hospitalisation, blood values, blood transfusion units, and range of motion. The second outcome of interest is to evaluate the accuracy of component positioning of robotic-assisted TKA compared to the conventional TKA.

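### Range of motion, listed in the primary outcome, may be read by staff who know the allocation; blinded retrieval of the reading does not protect it

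*Protocol article*

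**What the plan says.** The Introduction of the Protocol article gives the items of the primary outcome, among them "blood values, blood transfusion units, and range of motion". Outcomes of interests again places ROM among the items compared between the arms.

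Data to be collected describes the measurement. The examiner moves the limb through flexion and extension and reads a plastic pocket goniometer by the neutral-zero method. Readings fall on admission, on postoperative days 1 to 5 and "at each follow-up appointment by medical personnel who has not performed the index surgery". Nothing else is said about who reads.

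Randomisation and blinding makes three statements that bear on this:

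- Those who operate on or care for the patients know the arm.
- The handling of data is assigned to a separate pair: "Data curacy and collection will be conducted by two assessors blinded to group allocation and not involved in the clinical management of the patients".
- The assessors' task at the scheduled times is then worded as retrieval: "Assessors will retrieve patient data at the following follow-up times".

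The Discussion concedes that "the healthcare staff involved in the clinical management of the patients will not be blinded, increasing the risk of performance bias". It also says that patients learn their technique during the inpatient stay and links this to detection bias. It does not mention the person who reads ROM.

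**The concern.** Not having operated is a different condition from not knowing the arm. A colleague of the operator, a ward doctor or a treating physiotherapist could all meet the reader rule while belonging to the group that the blinding section leaves unblinded.

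Knowledge of the arm is also easy to acquire. Patients are allocated to surgeons who do one technique or the other, so the surgeon's identity reveals the arm. By the follow-up visits the patient knows the technique, and the discharge letter describes the operation.

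Passive ROM with a hand-held goniometer depends on the examiner, through how firmly the limb is moved and how the angle is rounded. If an expectation about robotic surgery shifts readings in one direction by arm, the trial could report a ROM difference that does not exist, on an item of its primary outcome. A larger sample does not help, because it shrinks the random error and leaves the bias in place.

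**Working it through.** **1. The sections side by side.**

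| Question | Data to be collected | Randomisation and blinding |
|---|---|---|
| Who handles ROM? | Medical personnel other than the operator | Two assessors outside clinical care, for data collection in general |
| Must that person be blinded? | Not stated | Yes for the assessors; clinical staff are unblinded |
| What is the act? | Moving the limb and reading the angle | Collecting and retrieving data |

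Two readings are possible. In the first, the assessors take the angle themselves and ROM is protected. In the second, staff take it and the assessors later retrieve the recorded value. Bias then enters before the blinded step and passes through it unchanged. The article does not settle which applies.

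**2. The plan's own figure.** The only sample size given is 198 per group, for WOMAC (difference 5, SD 20, power 80%, level 5%). It reproduces with a one-sided 5% level:

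n = 2 × (1.645 + 0.842)² × 20² / 5² ≈ 197.9, rounded up to 198.

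A two-sided 5% level would give 252. No sample size is given for ROM, so 198 enters below only as the number per arm.

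**3. Illustration of the size of the problem.**

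From the document: 198 per arm, an unpaired t-test, a null hypothesis of no difference and P < 0.05, taken as two-sided.

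Assumed, because the document gives no figure: a ROM SD of 8° to 20°; a systematic difference in reading between the arms of b = 1°, 2° or 3°, always in the same direction; and no true difference.

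Formulas (normal approximation):

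- SE = SD × √(2/198) = SD × 0.1005
- Smallest significant observed difference = 1.96 × SE
- False-positive risk = Φ(b/SE − 1.96) + Φ(−b/SE − 1.96)

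Worked case, SD 12° and b = 2°: SE = 1.21°; b/SE = 1.66; Φ(−0.30) + Φ(−3.62) ≈ 0.38.

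| SD | SE | Smallest significant difference | b = 0° | b = 1° | b = 2° | b = 3° |
|---|---|---|---|---|---|---|
| 8° | 0.80° | 1.58° | 5% | 24% | 70% | 96% |
| 10° | 1.01° | 1.97° | 5% | 17% | 51% | 85% |
| 12° | 1.21° | 2.36° | 5% | 13% | 38% | 70% |
| 15° | 1.51° | 2.95° | 5% | 10% | 26% | 51% |
| 20° | 2.01° | 3.94° | 5% | 8% | 17% | 32% |

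At this sample size an observed difference of 1.6° to 3.9° is already significant. Over the assumed SD range, a bias of 2° gives 17–70% and a bias of 3° gives 32–96%.

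**The case against.** The strongest reply is that no section says ROM readers know the allocation. The unblinded group is personnel involved in clinical management, the ROM readers are medical personnel, and nothing equates the two or bars the assessors from reading. This stands. A reader might infer that unblinded staff certainly take the readings; that is likely at the bedside on postoperative days 1 to 5, but the document does not state it.

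A reader might also infer that the protocol contradicts itself. It does not: measurement by staff and retrieval by blinded assessors can coexist. The sections are unreconciled, which is a weaker charge.

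The figures are open to challenge as well. Neither a bias of 2–3° nor any ROM SD appears in the document. Reader error that is unrelated to the arm adds noise and not bias, so the table applies only if readers err in one direction by arm. ROM is also one of several items in the primary outcome, and the trial is sized on WOMAC.

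It is tempting to go further and say that length of stay, another listed item, is distorted too, since "Patients shall be discharged when they shall have reach at least 80° of flexion". The document does not say that the study reading is the one used for discharge, and it gives no flexion distribution from which to size an effect. That step is not supported.

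Two replies fail. The Discussion's limitation covers performance bias from staff and detection bias from patients' awareness, not the ROM reader. Nor is this merely detail left to a fuller document: the article does fix who may read ROM, and the criterion it chooses does not protect the reading.

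**Conclusion.** The point holds as an unprotected measurement. A plan followed exactly as written allows ROM to be read by someone who knows the arm, and the blinded step that follows cannot correct this. Whether bias will occur, and how large it would be, cannot be determined from the document.

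If a one-directional bias of 2° to 3° did occur, the false-positive risk for ROM would be at least three times the nominal 5% across the whole assumed SD range (lowest value 17%). That statement rests on the assumed bias and SD, 198 per arm, a two-sided 5% test and no true difference. The reader rule should be changed because the change is cheap and specific, but the document does not show that the ROM result will be wrong.

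**What to change.** Amend Data to be collected so that it agrees with Randomisation and blinding:

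- One of the two blinded assessors already planned takes the study ROM reading at 6 weeks, 12 months and later visits, before opening the record and with the patient asked not to mention the technique.
- The rater is recorded for every reading.
- Readings on postoperative days 1 to 5, and any others not taken this way, are labelled open-label.
- The ROM conclusion rests on the blinded readings.
- The Discussion adds the remaining open-label readings to its detection-bias limitation.

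The cost is a short change of text and the scheduling of the assessors, with some follow-up readings missed or left open-label. Extending assessor readings to the ward would be far heavier: admission plus five postoperative days for 396 patients is 396 × 6 = 2,376 measurements. For that reason the inpatient readings are better labelled than restaffed. Because patients know their technique by follow-up, an assessor may still be told it, so the blinding will be good but not perfect.
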